## Abstract

Novel therapies capable of reducing myocardial infarct (MI) size when administered prior to reperfusion are required to prevent the onset of heart failure in ST‐segment elevation myocardial infarction (STEMI) patients treated by primary percutaneous coronary intervention (PPCI). Experimental animal studies have demonstrated that mineralocorticoid receptor antagonist (MRA) therapy administered prior to reperfusion can reduce MI size, and MRA therapy prevents adverse left ventricular (LV) remodeling in post‐MI patients with LV impairment. With these 2 benefits in mind, we hypothesize that initiating MRA therapy prior to PPCI, followed by 3 months of oral MRA therapy, will reduce MI size and prevent adverse LV remodeling in STEMI patients. The MINIMISE‐STEMI trial is a prospective, randomized, double‐blind, placebo‐controlled trial that will recruit 150 STEMI patients from four centers in the United Kingdom. Patients will be randomized to receive either an intravenous bolus of MRA therapy (potassium canrenoate 200 mg) or matching placebo prior to PPCI, followed by oral spironolactone 50 mg once daily or matching placebo for 3 months. A cardiac magnetic resonance imaging scan will be performed within 1 week of PPCI and repeated at 3 months to assess MI size and LV remodeling. Enzymatic MI size will be estimated by the 48‐hour area‐under‐the‐curve serum cardiac enzymes. The primary endpoint of the study will be MI size on the 3‐month cardiac magnetic resonance imaging scan. The MINIMISE STEMI trial will investigate whether early MRA therapy, initiated prior to reperfusion, can reduce MI size and prevent adverse post‐MI LV remodeling.

## Introduction

Coronary artery disease is one of the leading causes of death and disability worldwide,^1^ resulting in an estimated 7.3 million deaths per year.^2^ Despite major advances in the field of interventional cardiology, the mortality of ST‐segment elevation myocardial infarction (STEMI) remains high; in‐hospital mortality is approximately 5% to 6%, increasing to 7% to 18% at 1 year.^3^ In a large US registry consisting of 606 500 patients with acute myocardial infarction, heart failure (HF) was identified in 20.4% of individuals at admission, with a further 8.6% developing HF during the hospitalization itself.^4^ The onset of HF post‐STEMI is closely related to the final myocardial infarct (MI) size. For patients presenting with an acute STEMI, the most effective therapy for limiting MI size, preserving left ventricular (LV) function, and reducing the onset of HF is timely reperfusion using primary percutaneous coronary intervention (PPCI).^5^, ^6^, ^7^, ^8^

### Myocardial Reperfusion Injury as a Neglected Therapeutic Target

Although timely reperfusion is required to salvage viable myocardium in STEMI patients, the restoration of coronary blood flow in the infarct‐related artery has the potential in itself to induce cardiomyocyte death, a phenomenon that has been termed myocardial reperfusion injury and can contribute up to 50% of the final MI size.^9^ Therefore, novel therapies capable of protecting the heart from myocardial reperfusion injury may allow one to maximize the benefits of myocardial reperfusion in terms of MI size reduction. In this regard, the mineralocorticoid receptor antagonist (MRA) spironolactone may be beneficial.

### Mineralocorticoid Receptor Antagonist Therapy

Aldosterone, a mineralocorticoid receptor agonist, is synthesised primarily in the adrenal gland and is part of the renin‐angiotensin‐aldosterone system. It is known to regulate a number of pathophysiological pathways important to post‐MI HF, including inhibition of nitric oxide activity,^10^ acute endothelial dysfunction,^11^ increased vascular tone,^12^ vascular smooth muscle cell and cardiomyocyte necrosis,^13^, ^14^ myocardial hypertrophy and fibrosis,^15^, ^16^ apoptosis,^17^ and unfavorable LV remodeling.^18^ Consequently, a number of landmark clinical studies have highlighted the significant benefits of aldosterone antagonist therapy on clinical outcomes post‐MI.^19^, ^20^, ^21^

### Mineralocorticoid Receptor Antagonist Therapy to Target Myocardial Reperfusion Injury

Experimental preclinical data have demonstrated that administering MRA therapy by a clinically relevant regimen, using either intravenous potassium canrenoate (a compatible metabolite of spironolactone) or eplerenone, after a sustained episode of myocardial ischemia and 5 minutes prior to reperfusion, protected the heart against myocardial reperfusion injury and reduced MI size by 40% to 50% in murine, rat and rabbit in vivo models of MI.^22^ An earlier experimental study had reported a cardioprotective effect with the administration of eplerenone prior to the index ischemic event in the isolated perfused rat heart.^23^ A more comprehensive review of the cardioprotective effects of MRA therapy has been summarized in the review by van den Berg et al.^24^

Therefore, in this study we aim to combine the acute benefit of MRA therapy to reduce reperfusion injury and its benefit on preventing LV remodeling after 3 months of oral therapy. We hypothesize that early intravenous MRA therapy administered prior to reperfusion followed by 3 months of oral MRA therapy can reduce MI size and reduce adverse LV remodeling in STEMI patients.

## Methods

### Overall Study Design

The MINIMISE‐STEMI trial (https://clinicaltrials.gov, NCT01882179) is a proof‐of‐concept randomized clinical trial designed to investigate whether MRA therapy initiated prior to reperfusion and continued for 3 months can reduce MI size and prevent adverse LV remodeling at 3 months in STEMI patients treated by PPCI. It is a prospective, randomized, double‐blind, placebo‐controlled clinical trial that will recruit 150 patients through 4 tertiary care hospitals in the United Kingdom. The study will be conducted in accordance with the Declaration of Helsinki and has been approved by the National Research Ethics Service. All patients will provide informed written consent.

### Overall Objective

The main objective will be to investigate whether MRA therapy initiated prior to PPCI and continued for 3 months reduces MI size and prevents adverse LV remodeling in STEMI patients.

### Study Protocol

On immediate arrival at the hospital, patients presenting with an acute STEMI will be asked to give brief informed written consent to enter the MINIMISE‐STEMI trial and basic eligibility will be assessed. At coronary angiography, eligibility of inclusion into the trial (ie, proximal coronary artery occlusion and serum potassium (K^+^) <5.0 mmol/L and estimated glomerular filtration rate (eGFR) >30 mL/min/1.73m^2^) will be confirmed and patients will then be randomized to receive either MRA therapy or matching placebo. A detailed informed written consent will then be obtained on the ward following the PPCI procedure, within 24 hours after obtaining brief informed written consent, but before the patient is started on oral study medication. Blood tests will be taken to measure high‐sensitivity troponin T (hsTropT) and creatine kinase‐MB isoenzyme (CK‐MB) at the following time points pre‐PPCI and 6, 12, 24, and 48 hours post‐PPCI. In the first week following hospital admission, the patient will undergo a cardiovascular magnetic resonance imaging (MRI) scan (cardiovascular magnetic resonance [CMR], and this will be repeated 3 months later, after which the study ends. The overall study protocol is provided in the Figure 1.

**Figure 1 clc22401-fig-0001:**
[figure not shown]
Overall patient pathway. Abbreviations: CMR, cardiac magnetic resonance imaging; IV, intravenous; LVEF, left ventricular ejection fraction; MRA, mineralocorticoid receptor antagonist; PCI, percutaneous coronary intervention; STEMI, ST‐segment elevation myocardial infarction; TIMI, Thrombolysis In Myocardial Infarction.

### Patient Eligibility Criteria

All consecutive patients presenting with presumed acute STEMI in the 4 participating centers will be screened for eligibility. The inclusion and exclusion criteria are listed in Table 1.

**Table 1 clc22401-tbl-0001:** Patient Inclusion and Exclusion Criteria

Inclusion criteria for entry into trial (assessed on arrival at hospital)
Patients age >18 years
Patients presenting with acute STEMI and eligible for PPCI (as assessed by 12‐lead ECG; ST‐segment elevation ≥2 mm [0.2 mV] in ≥2 contiguous precordial leads or ≥1mm [0.1 mm] in ≥2 adjacent limb leads)
Presentation within 12 hours after symptom onset
Inclusion criteria for randomization (assessed in cardiac catheterization laboratory)
Angiographically proven proximal occlusion (TIMI: 0) of a major coronary vessel (LAD, LCX, RCA)
Normal serum K^+^ (<5.0 mmol/L)
Exclusion criteria for entry into trial (assessed on arrival at hospital)
Patients with known LVEF ≤40%
Participation in another trial
Cardiogenic shock (positive shock index OR need for catecholamine support OR SBP <90 mm Hg)
Killip class >2
Prior MI
Known compromised renal function (eGFR <30 mL/min/1.73 m^2^) or K^+^ >5.0 mmol/L
Current treatment with MRAs
Current treatment with cyclosporine
Pregnant or lactating females
Females of childbearing potential and males must be willing to use an effective method of contraception (hormonal or barrier method of birth control; abstinence) from the time consent is signed until visit 5, as per the guidance in the patient information leaflet
Allergies to IMP or its excipients
Known contraindication to CMR such as significant claustrophobia, severe allergy to gadolinium chelate contrast, presence of CMR‐contraindicated implanted devices (eg, pacemaker, ICD, CRT device, cochlear implant), imbedded metal objects (eg, shrapnel), or any other contraindication for CMR
Once the current sCr is known, patients with severely compromised renal function (eGFR <30 mL/min/1.73 m^2^) will also be excluded
Patients with known porphyria
Patients with significant liver dysfunction (INR >2)
Patients with known contraindications to treatment with spironolactone

Abbreviations: CMR, cardiovascular magnetic resonance imaging; CRT, cardiac resynchronization therapy; ECG, electrocardiogram; eGFR, estimated glomerular filtration rate; ICD, implantable cardioverter‐defibrillator; IMP, investigational medicine product; INR, international normalized ratio; K^+^, potassium; LAD, left anterior descending coronary artery; LCX, left circumflex coronary artery; LVEF, left ventricular ejection fraction; MI, myocardial infarction; MRA, mineralocorticoid receptor antagonist; PPCI, primary percutaneous coronary intervention; RCA, right coronary artery; SBP, systolic blood pressure; sCr, serum creatinine; STEMI, ST‐elevation myocardial infarction; TIMI, Thrombolysis In Myocardial Infarction.

### Randomization and Treatment Allocation

Eligible patients will be randomized via a Web‐based service (https://www.sealedenvelope.com) in a 1:1 manner to either MRA therapy or matching placebo. Randomization will be stratified by recruiting site. The patient, interventional cardiologist, caregivers, and data collector will be blinded to the treatment allocation. The study drug or placebo will be administered by the nonblinded research investigator.

### Study Drug and Placebo

#### 
MRA Therapy

Patients randomized to MRA therapy will receive an intravenous bolus of potassium canrenoate (200 mg, in keeping with the dose used initially by Hayashi et al^25^ and subsequently in the Aldosterone Blockade Early After Acute Myocardial Infarction [ALBATROSS] trial)^26^ followed by oral spironolactone 25 mg once daily for 2 weeks and then 50 mg once daily for the remaining 10 weeks, after which the MRA therapy will be stopped. Serum K^+^ will be checked at 2 and 4 weeks. Spironolactone will only be uptitrated to 50 mg after 2 weeks if the serum K^+^ is ≤5.0 mmol/L. If the serum K^+^ is 5.1 to 5.5 mmol/L, 25 mg spironolactone will be maintained, and if the K^+^ is >5.5 mmol/L, spironolactone will be discontinued.

#### Matching Placebo

Patients randomized to control will receive an intravenous bolus of normal saline followed by placebo control tablets for the 3 months, after which the placebo will be stopped. Serum K^+^ will be checked at 2 and 4 weeks.

### Optimal Heart Failure Treatment

The study protocol will ensure optimal medical therapy for all study participants according to current practice guidelines.^3^, ^27^, ^28^, ^29^ Therefore, patients with a left ventricular ejection fraction (LVEF) ≤40% on the initial CMR scan and evidence of HF or who have diabetes mellitus (DM) will be started on open‐label eplerenone according to current practice guidelines. These patients will be included in the intention‐to‐treat analysis.

### Cardiac Magnetic Resonance Protocol and Analysis

Each patient recruited into the MINIMISE‐STEMI trial will have 2 CMR scans, the first being performed in the week following hospital admission and the second performed at 3 months. Training in the CMR protocol will be provided to each recruiting site. All CMR scans will be analyzed by an independent MRI CoreLab at University College London.

The primary endpoint of MINMISE‐STEMI trial will be MI size on the 3‐month CMR scan (measured as the mass of late gadolinium enhancement (LGE) and expressed as a percentage of the LV mass). The CMR parameters that will be determined for the first CMR scan:
LVEF and indexed LV end‐systolic and end‐diastolic volumes and mass using short‐axis steady‐state free‐precession cine imaging.MI size, measured by the mass of LGE (10 minutes after administration of contrast) on CMR expressed as a percentage of LV mass.Area at risk (AAR), measured as the increase in T2 signal on‐T2 weighted images or T2 mapping, both of which have been validated against conventional measures of the AAR.^30^, ^31^, ^32^ The AAR will also be estimated using the modified Bypass Angioplasty Revascularization Investigation Myocardial Jeopardy Index (BARI) and Alberta Provincial Project for Outcome Assessment in Coronary Heart Disease (APPROACH) angiography scores.^33^
Myocardial salvage index = AAR − MI size/AAR. The myocardial salvage index (using T2‐weighted CMR and LGE) has been demonstrated to predict prognosis post‐PPCI.^34^
The incidence and extent of microvascular obstruction (hypo‐enhancement on LGE 20 minutes after administration of contrast).The incidence and extent of intramyocardial hemorrhage (hypo‐enhancement on Siemens T2* mapping sequence).

The CMR parameters that will be determined for the second CMR scan, at 3 months:
LVEF and indexed LV end systolic and diastolic volumes, wall thickness, and mass using short‐axissteady‐state free‐precession cine imaging.Final MI size, which represents the primary endpoint, measured by the mass of LGE and expressed as a percentage of the LV mass.

The CMR images will be analyzed by 2 experienced operators blinded to the treatment allocation and clinical outcome. Datasets will be reported in consensus, and advice from a third MRI operator will be sought in cases of disagreement (>5 g difference in infarct size between operators based on the limits of agreement for interobserver variability with the Otsu automated thresholding technique from Vermes et al).^35^ Left ventricular volumes and mass measurements will be calculated conventionally using dedicated software (CVI42 software, version 5.0.3; Circle Cardiovascular Imaging, Calgary, AB, Canada), with papillary muscles considered as part of the LV myocardium. Analysis of MI size and extent of myocardial edema will be performed using an in‐house macro written in ImageJ.^36^ The epicardial and endocardial borders will be manually traced and the areas of LGE will be quantified using the semiautomated Otsu detection method, as previously validated by Vermes et al.^35^ Any dark areas of hypo‐enhancement (microvascular obstruction ± intramyocardial hemorrhage) within the area of LGE will be included in the infarct area.^37^

### Study Endpoints

The primary endpoint of the MINIMISE‐STEMI study will be MI size quantified by LGE cardiac MRI performed at 3 months following hospital admission. The secondary endpoints are listed in Table 2. The safety endpoints will include major adverse cardiac events and side effects from MRA therapy (cardiovascular death, nonfatal MI, revascularization, hospitalization for HF, hyperkalemia, deterioration of kidney function, and need for dialysis; Table 3). Major adverse cardiac events will be reported after 3 months.

**Table 2 clc22401-tbl-0002:** Secondary Outcome Measures

Markers of myocardial reperfusion injury (myocardial blush grade, TIMI flow post‐PPCI, ST‐segment resolution at 90 minutes post‐PPCI)
Microvascular obstruction on CMR
Myocardial salvage (AAR by T2 imaging − final infarct size)
Acute myocardial infarct size (serum biomarkers and CMR on day 2–7)
Serum biomarkers (hsTropT, CK‐MB) at the following time points; 0, 6, 12, 24, and 48 hours post‐PCI (±1 hour)
LV remodeling on 3‐month CMR scan (index LVEDV and LVESV, LVEF, and LV mass and wall thickness)
Clinical outcome measures: CV death, nonfatal MI, revascularization, hospitalization for HF, hyperkalemia, deterioration of kidney function, need for dialysis

Abbreviations: AAR, area at risk; CK‐MB, creatine kinase MB isoenzyme; CMR, cardiovascular magnetic resonance imaging; CV, cardiovascular; HF, heart failure; hsTropT, high‐sensitivity troponin T; LV, left ventricular; LVEDV, left ventricular end‐diastolic volume; LVEF, left ventricular ejection fraction; LVESV, left ventricular end‐systolic volume; MI, myocardial infarction; PPCI, primary percutaneous coronary intervention; TIMI, Thrombolysis In Myocardial Infarction.

**Table 3 clc22401-tbl-0003:** Definitions of Safety Endpoints

CV death	Death due to a known CV cause or where the cause of death is unknown (ie, where no other cause of death has been identified from the medical history or an autopsy)
Nonfatal MI	Detection of rise and or fall of cardiac biomarkers with ≥1 value >99th percentile of the upper reference limit together with evidence of myocardial ischemia with ≥1 of the following: symptoms of ischemia; new ST‐T changes or new LBBB or development of pathological Q waves on the ECG; imaging evidence of new loss of viable myocardium or new regional wall‐motion abnormality
Revascularization	Any repeat PCI or CABG with or without valve within the first year postsurgery
Hospitalization for HF	Hospital admission of ≥24‐hour stay. HF will be judged to be present on symptoms (≥1 of the following: new or worsening dyspnea, orthopnea, or paroxysmal nocturnal dyspnea, or increasing fatigue/worsening exercise tolerance) and signs (1 of the following: new pulmonary edema by chest X‐ray in the absence of a noncardiac cause, crepitations believed to be due to pulmonary edema, and use of loop diuretics to treat presumed pulmonary congestion).
Hyperkalemia	Serum K^+^ level >5.5 mmol/L
Deterioration of renal function	sCr increase of >25% from baseline
Stroke	Stroke will be defined as a focal, central neurological deficit lasting >72 hours that results in irreversible brain damage or body impairment.

Abbreviations: CABG, coronary artery bypass grafting; CV, cardiovascular; ECG, electrocardiography; HF, heart failure; K^+^, potassium; LBBB, left bundle branch block; MI, myocardial infarction; PCI, percutaneous coronary intervention; sCr, serum creatinine.

### Statistical Analysis

A sample size of 50 in each group will have 80% power to detect a difference in means of 8.0 g infarct mass as assessed by MRI (the difference between a Group 1 mean, μ_1_, of 40.0 g, and a Group 2 mean, μ_2_, of 32.0 g), assuming that the common SD is 14.0 g infarct mass^38^ using a 2‐group *t* test with a 0.05 2‐sided significance level. However, we anticipate that about 10% of patients in the control group will have LVEF ≤40%, in which case they will receive the trial treatment as a matter of standard care. To allow for this dilution of the treatment effect, we have increased the sample size in each group to 62. If we further assume an attrition rate of approximately 15%, then 75 patients per group will be needed, for a total trial size of 150 patients.

Statistical analysis will be performed using SAS version 9.3 (SAS Inc., Cary, NC). The Fisher exact test will be used to compare categorical variables. Continuous variables will be compared with a mixed‐effects model to account for repeated measures. Primary data analysis will be performed in the intention‐to‐treat population, regardless of the treatment that was actually received. The results of as‐treated analyses for primary and secondary endpoints will also be calculated. Time‐to‐event analyses (secondary clinical endpoints), based on all available follow‐up data, will be performed with the use of Kaplan‐Meier estimates and be compared between groups with the use of the log‐rank test. A generalized linear model will be used to calculate risk ratios in the subgroup analyses and to test for interactions. After 75 patients have completed the trial, an interim analysis will be performed by the study statistician for safety reasons. The results will be evaluated by the data‐monitoring committee.

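### The 80% power is derived for infarct mass in grams, whereas the primary endpoint is infarct size as a percentage of LV mass, and nothing in the article links the two scales

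*Protocol article*

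**What the plan says.** The Protocol article defines the primary endpoint under Cardiac Magnetic Resonance Protocol and Analysis. MI size on the 3-month scan is "measured as the mass of late gadolinium enhancement (LGE) and expressed as a percentage of the LV mass", and the list of second-scan parameters repeats it: "Final MI size, which represents the primary endpoint, measured by the mass of LGE and expressed as a percentage of the LV mass". Study Endpoints names the same endpoint without a unit ("MI size quantified by LGE cardiac MRI performed at 3 months following hospital admission"), and the Abstract likewise gives none.

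The Statistical Analysis section plans in grams throughout. Fifty per group "will have 80% power to detect a difference in means of 8.0 g infarct mass as assessed by MRI". The control mean is given as "of 40.0 g, and a Group 2 mean" of 32.0 g follows it. The spread is fixed by "assuming that the common SD is 14.0 g infarct mass", with a two-group t test "with a 0.05 2‐sided significance level". The 50 per group then becomes 62 to allow for 10% dilution in the control group, and 75 to allow for about 15% attrition, 150 in total.

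No mean, SD or target difference in percent of LV mass appears anywhere in the article, nor does an LV mass with which to convert.

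**The concern.** Infarct mass and infarct mass divided by LV mass are different variables. The ratio has its own mean and SD, and its SD depends on how much LV mass varies between patients and how closely LV mass follows scar mass. LV mass is measured in each patient and is itself listed in Table 2 as a 3-month remodeling outcome, so it cannot be treated as a constant without argument. A power figure worked out in grams therefore need not hold for the ratio.

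The 80% and the whole chain from 50 to 62 to 75 per group rest on a variable other than the one named as primary. The result will be a difference in percentage points of LV mass, and no target has been stated on that scale. With grams in one section and a percentage in another, a reader could also question afterwards which scale was primary.

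**Working it through.** **Inputs from the Statistical Analysis section:** means 40.0 g and 32.0 g; difference 8.0 g; SD 14.0 g; two-sided alpha 0.05; two-group t test; dilution 10%; attrition about 15%.

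**1. Reproduce the plan in grams (noncentral t).**
- Standardised effect: d = 8.0/14.0 = 0.571. The sample size for 80% power is 49.05 per group, so 50; power at 50 is 80.8%.
- Dilution: 50/(1 − 0.10)² = 50/0.81 = 61.7, so 62. The diluted difference is 0.9 × 8.0 = 7.2 g; d = 7.2/14.0 = 0.514; power at 62 is 81.1%.
- Attrition: 62/0.85 = 72.9, so 73, against 75 stated. The difference is rounding in the cautious direction.

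The arithmetic is sound on the gram scale.

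**2. When the figure carries over.** If every patient had the same LV mass M, the difference and the SD would both be divided by M and d would stay at 0.571. It could also stay the same for particular combinations of LV-mass spread and correlation with scar mass. The article asserts none of these.

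**3. Range by the coefficient of variation (CV) of the ratio.** The plan's figures imply a relative reduction of 8.0/40.0 = 20%, or 18% after dilution, and a CV of 14.0/40.0 = 35%. *Assumption:* the 18% carries over to the percentage scale. Then d = 0.18/CV with 62 per group:

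| CV of % LV mass | d | Power |
|---|---|---|
| 30% | 0.600 | 91% |
| 35% | 0.514 | 81% |
| 40% | 0.450 | 70% |
| 45% | 0.400 | 60% |
| 50% | 0.360 | 51% |

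**4. Range by LV-mass behaviour.** *Assumptions:* LV-mass CV c of 10% to 25%; correlation ρ between scar mass and LV mass of 0 to 0.6; no treatment effect on LV mass. To first order, CV(ratio)² = 0.35² + c² − 2 × ρ × 0.35 × c. For example, c = 0.25 and ρ = 0 gives √(0.1225 + 0.0625) = 0.43, so d = 0.18/0.43 = 0.42 and power is 64%.

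| LV-mass CV | ρ = 0 | ρ = 0.3 | ρ = 0.6 |
|---|---|---|---|
| 10% | 78% | 85% | 91% |
| 15% | 74% | 84% | 93% |
| 20% | 69% | 82% | 94% |
| 25% | 64% | 78% | 94% |

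Seven of the twelve cells are above 80% and five are below. No LV-mass CV, correlation or percentage-scale SD used here comes from the article.

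**The case against.** The strongest reply is that nothing has been shown to be lost. The sums are correct, many plausible combinations of LV-mass spread and correlation leave power at or above 80%, and the correction asks for no more patients. That stands: the tables do not show that the trial is underpowered, and a reader who infers this from the lower cells goes further than the document allows. It is equally unsupported to say that the 80% holds, because the article gives no figure on the scale of the endpoint.

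A second reply is that an article condenses a fuller protocol. It does not answer this point, because the article does not defer the calculation. It gives the difference, means, SD, test, alpha, dilution and attrition in full, in a unit other than the one it fixes for the endpoint.

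Three further inferences are tempting and should not be drawn:
- That the reader-disagreement limit (">5 g difference in infarct size between operators") is part of the same fault. It is a quality-control limit on the measured numerator, tied to interobserver limits from a cited validation study, and is compatible with a ratio endpoint.
- That the planning figures come from the wrong scan time. The scan day behind the SD belongs to a cited source that is not at hand.
- That a null result could not be interpreted. A confidence interval can be read without a planning difference, the plan implies a 20% relative target, and LV mass is measured at 3 months, so the gram result can be set beside the 8.0 g target.

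Finally, the power figures above are for a t test, while the same section says that continuous variables will be compared with a mixed-effects model. They are indicative only.

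**Conclusion.** The inconsistency holds. The article names infarct size as a percentage of LV mass as primary and powers infarct mass in grams, without a conversion or an argument that the standardised effect is the same. The gram-scale figures are right but belong to a different variable.

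The direction of the discrepancy is unknown. If the 18% diluted reduction carries over, power with 62 per group runs from 91% to 51% for CVs of 30% to 50%. Under the assumed LV-mass CVs of 10% to 25% and correlations of 0 to 0.6, it runs from about 64% to 94%. The supportable conclusion is that the stated 80% need not apply to the primary endpoint and that the article gives no means of telling whether it does.

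**What to change.** Keep 150 patients. Restate the calculation in percentage points of LV mass at 3 months, giving the power and the detectable difference for 62 evaluable per group. Take the mean and SD in percent of LV mass from the cited source if it reports them. Otherwise use a blinded pooled SD from the core-lab reads, which needs no unblinding.

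Show a range with it, because few patients are available: Study Timeline gives 24 enrolled. If 24 three-month scans gave a CV of 35%, the approximate 95% interval (chi-square, 23 degrees of freedom) would be 27% to 49%, which by the formula in step 3 corresponds to power of about 95% down to 53%.

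Alternatively, before unblinding, align the endpoint definition and the planning scale so that one unit is used in both sections. The reader-disagreement limit in grams can stay as it is.

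The cost is one recalculation and a reworded paragraph, with no extra patients. The downside is that the stated power may become less favourable.
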